### 2.4. Study Procedures

The recruitment period was planned from April 2021 to December 2023. Depending on risk stratification, patients undergo 18–49 visits, including the screening and the 12 follow-up visits (one every 3 months over the 36-month follow-up period).

At screening, the following data are collected: demographic and clinical characteristics; physical examination findings; disease-specific data (histological subtype, stage, number of involved nodal areas, extranodal involvement); patient breakdown according to mEORTC criteria; laboratory test results, Eastern Cooperative Oncology Group (ECOG) performance status; and functional test results, including pregnancy testing.

At treatment visits, the following data are collected: all changes in symptoms, physical examination, laboratory results; treatments administered; and adverse events. Pregnancy is verified at each treatment visit.

Collected information data during follow-up visits include date and extension of relapse in case of treatment failure; subsequent lymphoma treatment; secondary malignancies, cardio-vascular disease, and other organ toxicity; and survival.

Patients achieving complete metabolic response (CMR) on both PET-2 and end-of-treatment PET (EoT-PET) by blinded independent central review (see below) will undergo routine follow-up: clinical and laboratory evaluations every 3 months for the first 3 years, and additionally, a cfDNA assay (every 3 months during the first year, and every 6 months during the second year). PET imaging is performed only when indicated by clinical symptoms or laboratory abnormalities. If PET suggests HL relapse, a biopsy is strongly recommended to confirm the diagnosis of disease recurrence. Patients meeting criteria for limited relapse are included in group 2 and receive “delayed” INRT followed by nivolumab 240 mg every 14 days for 1 year.

Routine clinical data will be documented at study sites and entered into a secure, web-based electronic case report form (eCRF) system (The diCELLa eCRF Clinical Trials platform) (https://dicella.com/ecrf/ assessed on 14 August 2026). Documentation is sourced from routine medical records and verified for completeness through centralized and on-site monitoring by medical managers and clinical monitors. Imaging data and cfDNA are integrated with clinical data in the eCRF.

The imaging schedule in the RAFTING trial includes baseline PET for staging, interim PET after two cycles of chemotherapy (PET-2), PET at the end of chemotherapy (EoC-PET), and PET at the end of treatment (EoT-PET). In LR group 1a patients, PET-2, EoC-PET, and EoT-PET correspond to the same scan. In LR group 1b patients, EoC-PET coincides with EoT-PET. In high-risk (HR) or relapsed patients, EoT-PET is performed after completion of nivolumab therapy. Thus, the timing of EoT-PET depends on the risk group and treatment duration.

Response is assessed using the Lugano 2014 Response Criteria [17] for chemotherapy-treated patients and LYRIC criteria for those receiving nivolumab [18].

All PET/CT examinations are performed according to the imaging governance framework established by the Cuneo Core laboratory (CoreLab) to ensure analytical validity, reproducibility, and quantitative comparability of PET-derived measurements across participating centers. Participating centers are required to use PET/CT scanners that have successfully completed the FIL Clinical Trial Qualification (CTQ) program. Scanner qualification is based on standardized phantom calibration procedures using 18F-filled cylindrical phantom reference sources, ensuring harmonization of standardized uptake value (SUV) measurements across scanners and institutions [19]. Patient preparation, radiotracer administration, uptake time, acquisition parameters, and image reconstruction are performed according to international procedural standards consistent with EANM guidelines for PET/CT imaging [20]. Compliance with protocol-defined acquisition parameters is verified through automated quality control procedures implemented within the web-based imaging platform [21].

PET images acquired at baseline, PET-2, and EoT-PET are uploaded via the platform for image exchange and review Web-Based Imaging Diagnosis by Expert Network (WIDEN) [22]. Centralized image interpretation is conducted through a blinded independent central review (BICR) performed by three experienced nuclear medicine physicians. Reviewers were blinded to clinical information and treatment allocation.

Baseline TMTV was measured independently by two central nuclear medicine reviewers on baseline PET images using semi-automated lesion segmentation software (Fiji—petctviewer.org, software version 1.53–1.54). All lymphoma-related fluorodeoxyglucose (FDG)-avid lesions were identified and segmented using a threshold corresponding to 41% of each lesion’s SUVmax [22]. If needed, lesions were edited by the operator to exclude uptake unrelated to lymphoma or to include lesions not captured by the automatic segmentation process. Physiological uptake and non-lymphomatous FDG-avid findings were excluded by expert visual review, and the metabolic volumes of all lesions were summed to derive whole-body TMTV.

Inter-reader TMTV agreement was assessed using the percentage difference between the two measurements and their mean value in relation to the prespecified 84 mL stratification threshold. When the percentage difference was <10% and the mean TMTV was between 71 and 97 mL, the mean of the two measurements was assigned as the final TMTV. When the percentage difference was <20% and the mean TMTV was either <71 mL or >97 mL, the mean value was likewise assigned. In all other cases, CoreLab reviewed the lesion segmentations and corresponding RT structures to identify the source of disagreement and then performed a consensus assessment.

PET-2 scans were independently reviewed by experienced central readers using the Deauville five-point scale. A final PET-2 classification was assigned when at least two reviewers reached concordant conclusions. If agreement was not achieved, an additional independent review was requested. The Imaging CoreLab evaluated the source of disagreement, including lesion identification, reference-organ assessment, image quality, and response categorization. Selected unresolved cases underwent consensus review [23]. The final centrally assigned PET-2 result was used for treatment allocation. PET-2 scans with Deauville scores 1–3 were classified as negative, whereas scores 4–5 were considered positive (DS 4: uptake of the reference lesion (RL) moderately higher than liver uptake; DS 5: uptake of the reference lesion higher than the liver uptake and calculated as follows: SUVmax RL > 2x SUVmax of the liver).

In patients treated with nivolumab, the final (end-of-treatment) PET/CT was scheduled approximately four weeks after the last nivolumab dose. According to the protocol, this assessment was to be interpreted using the LYRIC criteria. In the case of an indeterminate response (IR), the PET/CT scan is reviewed in consensus by the reviewers to confirm IR. PET/CT in follow-up is recommended only in the following situations: clinical suspicion of relapse (appearance of symptoms or new findings on physical examination); reappearance of cfDNA after previous negative result; a 2-log increase in cfDNA in the blood.

CfDNA is measured at baseline and after two chemotherapy cycles (PET-2) in all patients. In addition, in LR patients entering CMR, cfDNA is assessed every three months during the first year and every six months during the second year.

Peripheral blood samples (20 mL) are collected in cell-free DNA BCT tubes (Streck) and centralized at the Institute of Oncology Research ([name] Lab). Plasma is processed to obtain at least 30 ng of cfDNA (~5000 genome equivalents), and germline genomic DNA (gDNA) is isolated from peripheral blood mononuclear cells. Longitudinal assessment of cfDNA for genotyping and residual disease quantification is performed using the LyV4.0 CAPP-seq assay (Cancer Personalized Profiling by Deep Sequencing) (CAPP-seq) [24]. The assay targets 344 kb of genomic space, including 33 Activation-Induced Cytidine Deaminase (AID)-associated somatic hypermutation (SHM) noncoding regions [25,26,27] and coding regions of 155 recurrently mutated genes in mature B-cell tumors. A complete list of the targeted genes and genomic regions, together with the analytical validation of the assay, has been previously reported (Pirosa et al., Supplementary Material) [24].

To ensure genomic fidelity and mitigate batch biases, patient-derived cfDNA and matched gDNA were sequenced simultaneously. Sequencing was performed on the Illumina NextSeq500 platform (paired-end, 2 × 150 bp). This paired approach, combined with background-error suppression models derived from healthy cohorts, enabled the precise isolation of true somatic mutations while filtering out inherited polymorphisms and sequencing artifacts (detailed bioinformatics and laboratory methodologies are described elsewhere).

The limit of blank (LoB) was first established from the distribution of background variant allele frequencies observed in 119 post-treatment cfDNA samples from patients cured of lymphoma (blank samples). The limit of quantification (LoQ) was then calculated as LoB + 10 × standard deviation (LoB), thereby defining the lowest variant allele frequency that could be reliably quantified above background noise. Conversely, the limit of detection (LoD) for residual cfDNA was assessed by serial dilution experiments using diagnostic cfDNA samples mixed with cfDNA from healthy donors.

A critical feature of this protocol is the assay’s analytical sensitivity of 0.1%, determined through serial dilution experiments during assay validation [24]. This level of sensitivity, achieved through targeted enrichment and ultra-deep sequencing with a minimum of 2000× coverage across ≥80% of target regions, enables the reliable detection of very low-frequency tumor-derived variants. This ultra-high sensitivity is essential for accurately evaluating minimal residual disease (MRD) and detecting molecular relapse prior to radiographic or clinical progression.

Bioinformatic analysis includes alignment to the reference genome and somatic variant calling by comparison with matched gDNA. Multiple error-suppression steps are applied, including statistical filtering and comparison with background cfDNA data from healthy individuals, to ensure high specificity.

cfDNA concentration is calculated by multiplying the cfDNA concentration in plasma (pg/mL) by the mean allele fraction of patient-specific reporter mutations and dividing by 3.3 (pg per haploid genome equivalent) and is expressed on a log10 scale.

Within this study protocol, negative MRD was defined as the complete clearance of all baseline somatic alterations—including missense substitutions and short indels—to levels below the assay’s limit of quantification, as previously established during assay validation [25].

PET/CT in follow-up is recommended in the following cases: clinical suspicion of relapse (symptoms or new findings on physical examination); reappearance of cfDNA after previous negativization; a 2-log increase in cfDNA in the blood.

### 2.5. Sample Size

The sample size calculation was based on the following assumptions: the anticipated 3-year progression-free survival (PFS) rate for stage I–IIA non-bulky eHL patients with a negative PET-2, treated with CMT, is 94% [6]; the expected 3-year PFS for PET-2-negative patients with similar clinical characteristics, treated with chemotherapy alone comprising two to four courses of chemotherapy, ranges between 87% and 93%, as reported in three prospective and one retrospective clinical trials, despite variations in patient characteristics and treatment intensity [6,7,8,28].

The expected 3-year PFS for PET-2-negative patients with TMTV < 84 mL treated with chemotherapy alone is anticipated to be at least 90%. In this context, a one-sample non-inferiority design was employed to calculate the sample size required to test whether the proportion of low-risk eHL patients, treated with chemotherapy alone, alive and disease-free at 3 years, is non-inferior to that of patients treated with CMT. For the non-inferiority assessment of the primary endpoint, we assumed an expected true response proportion of 90%. The non-inferiority historical reference value was set at 95%, reflecting the historical outcome of CMT reported in trials such as RAPID and H10, with an absolute non-inferiority margin of 10 percentage points; thus, non-inferiority would be concluded if the response proportion in the study population exceeds 85%.

To define the sample size of patients to be enrolled, we used a one-sided type I error of 0.20 and type II error of 0.20 (80% power). “The one-sided α of 0.20 was prespecified because the study was designed as an exploratory Phase 2 screening trial, in which minimizing false-negative findings was prioritized over controlling false-positive findings, consistent with the recommendations of Rubinstein et al.” [29].

A total of 102 low-risk (defined by a low MTV and a negative PET-2) eHL patients should be enrolled to exclude a difference between the true proportion and the comparison value of at least 10%. Considering an expected 75% of patients with a negative PET-2 and low TMTV, and a drop-off rate of 15%, 160 patients had to be enrolled in the trial.

In the exploratory phase 2 setting, a one-sided α = 0.20 was chosen because the potential harm of a false negative result (failing to recognize an effective treatment) is considered more significant than that of a false positive result (proceeding to confirmatory testing) [29].

### 2.6. Statistical Methods Used to Compare Groups for Primary and Secondary Outcomes

The primary efficacy endpoint is 3-year progression-free survival (PFS) in the LR group, which will be evaluated for non-inferiority relative to a prespecified historical control rate. The PFS in the LR group is defined as the time from LR patient registration to the first occurrence of disease progression (limited or extended relapse) or death for any reason. The PFS distribution will be estimated using the Kaplan–Meier product-limit method, and the standard error of the 3-year survival estimate will be computed using Greenwood’s formula. For the primary hypothesis, a one-sided 80% confidence interval (CI) for the 3-year PFS rate will be constructed. Non-inferiority will be concluded if the lower bound of this one-sided 80% CI exceeds 85%, corresponding to a one-sided type I error rate (alpha) of 0.20.

The first secondary endpoint is also used for LR patients only. The 3-year freedom from second treatment failure (FF2TF) is calculated for LR who have limited relapse only and are rescued according to the protocol. It is measured from registration to the date of second relapse (during or after RT followed by nivolumab) (extended relapse) or death for any reason. FF2TF will be estimated using the Kaplan–Meier method, and the 3-year FF2TF estimate will be reported with a two-sided 95% confidence interval (CI) derived using Greenwood’s formula.

The second secondary efficacy endpoint is the 3-year PFS in the HR cohort, defined as the time from HR patient registration to the first occurrence of disease progression (extended relapse) or death for any reason. The 3-year PFS estimate will be obtained from the Kaplan–Meier curve, with a two-sided 95% CI calculated using Greenwood’s formula.

Both secondary assessments will allow us to calculate 3-year event-free survival (EFS) across the entire study cohort. The EFS is defined as the time from patient registration to the failure of the planned study treatment, which varies by study groups and includes only extended relapses or death for any reason. This is considered one of the most important study aims, reflecting the efficacy of a flexible-intensity and personalized treatment offered to different eHL prognostic groups. The 3-year EFS estimate will be obtained from the Kaplan–Meier curve, with a two-sided 95% CI calculated using Greenwood’s formula.

The third secondary endpoint is 3-year overall survival (OS) of the entire cohort of patients enrolled into the study, defined as time from patient registration to death for any reason. The OS will be estimated using the Kaplan–Meier method, with a two-sided 95% CI based on Greenwood’s standard error.

As this is a single-arm evaluation, analyses of the secondary endpoints will be descriptive and will report point estimates with corresponding measures of precision, without formal hypothesis testing against a concurrent comparator. The summary of the study outcomes is presented in Table 1.

Finally, the diagnostic performance of cfDNA for detection of an impending relapse during follow-up in LR group patients will be summarized using overall accuracy, sensitivity, specificity, negative predictive value, and positive predictive value. Each metric will be presented as a point estimate with a two-sided 95% CI computed using the Clopper–Pearson exact method.

As an intention-to-treat (ITT) approach is preferred for phase III randomized clinical trials and a per protocol (PP) approach is preferred for equivalence and non-inferiority trials, a PP analysis will be preferred for assessing the primary study endpoint of treatment efficacy in LR patients, and an ITT approach will be used as secondary [30]. For all the other study endpoints in the RAFTING study, both an ITT and PP will be used.

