### 2.3. Patient Stratification and Treatment

Stratification is performed in two steps to define the low- and high-risk categories.

The first is based on the TMTV value at baseline (low or high) and presence/absence of modified EORTC (mEORTC) criteria, in which the classical bulky disease (defined as a nodal mass larger than 10 cm) is replaced by a “large nodal mass” (LNM) of 5–10 cm in diameter (Figure 1). The second step is after the second chemotherapy cycle and is based on PET-2 results.

The low-risk (LR) group is defined by a baseline TMTV < 84 mL and negative interim PET-2 (Deauville scale; DS: 1–3). Within this category, patients are further split into two more categories: group 1a—patients without mEORTC risk factors that receive two chemotherapy cycles only, and group 1b—patients with at least one risk factor according to the mEORTC criteria that receive four chemotherapy cycles (Figure 2). The ABVD chemotherapy includes doxorubicin 25 mg/m^2^, bleomycin 10 IU/m^2^, vinblastine 6 mg/m^2^, and dacarbazine 375 mg/m^2^, administered intravenously on days 1 and 15 of each 28-day cycle.

The HR group includes patients with either a positive PET-2 (DS 4–5, group 3a) and/or baseline TMTV ≥ 84 mL (group 3b). Both patient subsets receive a “triple therapy,” consisting of four chemotherapy cycles, INRT at either 20 or 30 Gy depending on the absence or presence of baseline mEORTC risk factors, respectively, followed by Nivolumab maintenance administered every two weeks at a dose of 240 mg intravenously over 30 min for up to one year, for a maximum of 24 doses (Figure 2). This duration was selected based on the CheckMate 205 and KEYNOTE-087 studies [12,13]. The newly diagnosed advanced-stage HL patients (CheckMate 205 study, group D) received up to 16 doses of nivolumab (4 doses of monotherapy and 12 in combination with AVD chemotherapy). The relapsed/refractory patients received nivolumab up to disease progression or unacceptable toxicity, with a possibility of treatment discontinuation in group C for patients with CR for 1 year. In both cases, acceptable CR rate and duration were achieved. The KEYNOTE-087 data show that 1 year of PD-1 blockade is associated with sustained remissions [14]. Recognizing that the optimal duration of anti-PD-1 therapy in this setting remains unknown, this study will explore correlations between treatment duration, toxicity, and outcomes to inform future trials.

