**Figure 2 biomedicines-14-01861-f002:**
[figure not shown]
Study treatment scheme. ABVD—doxorubicin, bleomycin, vinblastine, dacarbazine, Gy—Gray, INRT—involved node radiation therapy, mEORTC—modified EORTC criteria, PET-2—positron emission tomography after second chemotherapy cycle, TMTV—total metabolic tumor volume.

**Table 1 biomedicines-14-01861-t001:** The summary of study outcomes.

End-Point	Type	Group of Patients	Events
3-year progression-free survival (PFS) in low-risk group	Primary	Low-risk	Any progression (limited and extended relapse—whatever occurs first); death of any reason
3-year freedom from second treatment failure (FF2TF)	Secondary	Low-risk with limited relapse rescued in protocol (radiation therapy + nivolumab)	Progression during or after rescue treatment (extended relapse); death of any reason
3-year progression-free survival (PFS) in high-risk group	Secondary	High-risk	Extended relapse; death of any reason
3-year event-free survival (EFS)	Secondary	Entire cohort	Extended relapse (failure of planned per-protocol treatment—varies depending on stratification); death of any reason
3-year overall survival (OS)	Secondary	Entire cohort	Death of any reason

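### FF2TF is counted from registration in patients selected by a later limited relapse and rescue, so the 3-year figure overstates how well rescue works

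*Protocol article*

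**What the plan says.** Section 2.6 of the protocol article sets out FF2TF as the first secondary endpoint.

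- **Population.** It "is calculated for LR who have limited relapse only and are rescued according to the protocol". Table 1 gives the same restricted set: "Low-risk with limited relapse rescued in protocol (radiation therapy + nivolumab".
- **Time origin.** "It is measured from registration to the date of second relapse".
- **Events.** Table 1 lists "Progression during or after rescue treatment (extended relapse); death of any reason".
- **Estimate.** Kaplan–Meier, and "the 3-year FF2TF estimate will be reported with a two-sided 95% confidence interval (CI", with Greenwood standard errors and no hypothesis test.

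Entry to the rescue group happens during follow-up. Section 2.4 says "Patients meeting criteria for limited relapse are included in group 2" and describes no new registration at that moment. The Introduction names rescue of low-risk failures by radiotherapy plus nivolumab as something the study aims to determine.

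**The concern.** The population is fixed by something that happens after time zero. To be counted, a patient must have reached a limited relapse alive and gone on to rescue. A second relapse cannot come before the first, and a patient who died before rescue is not in the set. Everyone in the analysis therefore carries a stretch of guaranteed event-free time from registration to relapse, and the Kaplan–Meier curve counts it as success.

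A patient who relapses at month 30 brings 6 months of experience after relapse to a figure labelled 3-year. Section 2.3 gives nivolumab for up to one year after radiotherapy, so that patient could still be on rescue at the time point. The estimate mixes how late the first relapse came with how well rescue worked.

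FF2TF is the only listed endpoint specific to rescue. The Discussion presents the rescue strategy as a possible way to avoid high-dose chemotherapy and transplantation. An inflated figure would support that argument more strongly than the data do.

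**Working it through.** **The plan's own figures.** The article states no FF2TF figure. Its sample size (Section 2.5) reproduces:

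- n = p1(1−p1)(z0.80+z0.80)²/(p1−p0)², with p1 = 0.90 and p0 = 0.85: 0.09 × (0.8416+0.8416)² / 0.0025 = 102.0.
- 102 / 0.75 / 0.85 = 160.0.

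Neither figure involves FF2TF.

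**Direction.** Let T be the time in years from registration to limited relapse, and S(u) the probability of being free of failure u years after relapse. On the registration clock, a patient relapsing at T is event-free at 3 years with probability S(3−T). The 3-year rescue value is S(3). Because S never rises, S(3−T) is at least S(3) for any failure pattern. The two are equal only if no failures fall between 3−T and 3 years after relapse.

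**Size.** The documents give neither T nor S, so both are assumed. With exponential failure and true 3-year control S, the reported value is S^((3−T)/3). At S = 0.50 and T = 1, this is 0.50^(2/3) = 0.630.

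| True 3-year control after relapse | T = 6 mo | T = 12 mo | T = 18 mo | T = 24 mo |
|---|---|---|---|---|
| 30% | 36.7% | 44.8% | 54.8% | 66.9% |
| 50% | 56.1% | 63.0% | 70.7% | 79.4% |
| 70% | 74.3% | 78.8% | 83.7% | 88.8% |
| 80% | 83.0% | 86.2% | 89.4% | 92.8% |

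The inflation runs from 3 points (80%, relapse at 6 months) to 37 points (30%, relapse at 24 months). If relapses are spread evenly over months 3 to 36, a true 50% is reported as 74% and a true 70% as 85%; mean observation after relapse by month 36 is then (36−3)/2 = 16.5 months.

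**Number of patients.** Section 2.5 expects 90% of low-risk patients to be event-free at 3 years. The Introduction cites 12.6% relapse after radiation-free treatment in H10, with 73% of relapses confined to the initially involved regions. Taking that 73% as a stand-in for limited relapse:

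- 102 × 0.10 × 0.73 = 7.4
- 102 × 0.126 × 0.73 = 9.4

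So about 7 to 9 patients. The trial's definition of limited relapse also allows up to three new nodal sites, so this is a rough guide.

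**The case against.** **Registration might mean entry to the rescue group.** Nothing in the article supports this. No re-registration at relapse is described. Section 2.6 also says the secondary assessments feed into event-free survival, which runs from patient registration.

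**A registration clock can be coherent.** That is right if all low-risk patients form the denominator. The result then describes the whole strategy, not the rescue. The defect is the pairing of clock and population, and either could be changed.

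**The consequence is limited.** This stands. Secondary endpoints are descriptive. With 7 to 9 patients the interval will be very wide: exact 95% limits are roughly 29–96% for 5 of 7 event-free and 30–93% for 6 of 9. FF2TF is also not the only information on rescue. Event-free survival counts later extended relapse in the whole cohort, and the interim rule in Section 2.9 looks at second relapses among low-risk patients. But a wide interval does not correct a bias, and neither of these isolates patients who were rescued.

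**The size is assumed.** This also stands. If failures come soon after rescue, or first relapses come early, the inflation is small.

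**Stronger readings that the documents do not support.** A reader might infer that low-risk PFS has the same flaw, because low-risk status needs a negative PET-2. The article counts it as "time from LR patient registration to the first occurrence of disease progression", which may mean trial entry or assignment to low risk after PET-2. On the second reading there is no shift. On the first, the guaranteed time is about 56 days (two 28-day cycles), and with a constant hazard 85.0% becomes 0.85^((3−56/365.25)/3) = 85.7% and 90.0% becomes 90.5%. Any effect on the non-inferiority claim also depends on the time origin of the historical rate, which is not given.

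A reader might also infer that the nivolumab-duration analysis is biased. The article says only that "this study will explore correlations between treatment duration, toxicity, and outcomes to inform future trials". It fixes no method, and bias would arise only if duration were handled as a baseline variable.

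**Conclusion.** The point holds for FF2TF. As written, the endpoint pairs a population defined by a later event with a clock that starts before that event, and the 3-year value is biased upward as a measure of rescue efficacy. The direction follows from the definition alone.

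The size rests on assumed relapse timing and on exponential failure after rescue, unrelated to when the first relapse came. Over relapse at 6 to 24 months it is about 6 to 29 points at a true 50%, and 4 to 19 points at a true 70%.

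The primary non-inferiority test, the 85% threshold and the sample size are untouched. The finding does not extend to low-risk PFS, where only the start date needs clarifying, or to the nivolumab-duration exploration.

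**What to change.** - **Time zero and population.** In Section 2.6 and Table 1, define FF2TF from the date of confirmed limited relapse, or from the start of rescue radiotherapy, to second relapse or death. Include all low-risk patients who start rescue, whether or not they complete it. Starting at rescue radiotherapy matches that population exactly; starting at relapse leaves a short guaranteed interval between relapse and rescue.
- **Reporting.** Give the estimate at 12 and 24 months after time zero, with the number at risk at each.
- **If a from-registration curve is kept.** Either use delayed entry at relapse, accepting very small early risk sets, or use all low-risk patients as the denominator and count first extended relapse as an event. Label the latter a strategy endpoint, not rescue efficacy.
- **Clarification only.** State whether LR patient registration means trial entry or assignment to low risk after PET-2.

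The change is one of wording. Relapse dates and treatments given are already collected (Section 2.4), and follow-up is still under way. The cost is a less favourable and less mature figure: few of the roughly 7 to 9 expected patients will reach 36 months after rescue.
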